### Study participants and eligibility criteria

Individuals over 75 years of age admitted to the Department of Geriatrics of the Complejo Hospitalario de Navarra between March 2015 and March 2017.

The inclusion criteria are:Age: 75 years or older.Able to ambulate with or without personal/technical assistance.Barthel Index ≥60Able to communicate.Informed consent: Must be capable and willing to provide consent.

The exclusion criteria are:–Duration of hospitalization < 6 days.–Any factor precluding performance of the physical training programme or testing procedures as determined by the attending physician. These factors include, but are not limited to the following:Terminal illness.Myocardial infarction in the past 3 months.Unstable cardiovascular disease or other medical condition.Upper or lower extremity fracture in the past 3 months.Severe dementia (GDS 7).Unwillingness to either complete the study requirements or to be randomized into the control or intervention group.

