Muscle strength and aerobic capacity decrease rapidly as a result of immobilization. After only ten days of rest, a healthy elderly person can lose 12–14 % of their VO_2max_ and muscle strength in the lower extremities [29]. In addition, skeletal muscle power decreases more rapidly than muscle strength with advancing age [30] and is also strongly associated with functional outcomes and functional capacity in elderly individuals at risk of disability [31, 32]. At the muscular level, reduced muscle use is associated with myofibrillar protein loss, muscle atrophy, and impaired control of the recruitment of motoneurons; at the clinical level, reduced muscle use is associated with decreased coordination, muscle strength, power output, aerobic capacity, balance, and exercise tolerance [5]. The consequences usually extend over time, and may produce long-term effects [30].

Alternative care models for an emphasis on multidisciplinary and continuing care units are currently being developed. Their main objective, other than the recovery of the condition that caused admission [32], is the prevention of functional decline. Many studies on functional decline have discussed the available evidence regarding the effectiveness of acute geriatric units [33, 34]. Despite the theoretical support for the idea that mobility improvement in the hospitalized patient carries multiple benefits, this idea has not been fully translated into clinical practice, and some studies have found paradoxical results [35]. The new models include exercise as an essential part of conventional treatment, at least when the patients are discharged to their homes [36]. Simple and basic procedures such as increasing the walking duration by 12 min or daily slow walking can reduce the average hospital stay [37]. In all of these circumstances, a comprehensive geriatric assessment of this type of patient should also consider the close link between the functional and cognitive situations, in addition to the previous theoretical concepts [38].

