Exercise and early rehabilitation programmes are among the mechanisms by which functional and cognitive decline is prevented during hospitalization. Although risk factors associated with hospitalization and functional decline after discharge have been intensively studied, few randomized clinical trials have examined the potential benefits of conducting standard exercise programmes for hospitalized acute elderly medical patients. Nevertheless, the theoretical framework allows us to grasp the scope of possible improvement that exists for this population sector when such interventions are applied properly and selectively. The benefits of exercise have been clinically, biologically and even economically confirmed [39, 40], making exercise part of the therapeutic arsenal at our disposal. Multicomponent programs, and especially resistance exercise that includes muscle power training, are currently the most relevant interventions to slow down disability and other adverse outcomes, but these programmes have not been tested in acute geriatric patients. Moreover, to be effective, exercise has to be prescribed with a progressive individualized plan, similar to other medical treatments [31]. Some prospective studies have previously shown that hospitalization of older adults in a suitable environment can reduce disability and enhance the recovery of compromised activities during and after the acute event, which is contrary to some theories that highlight only the negative aspects or removal from the living environment [41].

The Cochrane reviews regarding exercise for acutely hospitalized elderly medical patients included only seven randomized controlled trials and two controlled clinical trials out of 3138 potentially relevant articles; the effect of exercise on measures of functional outcome was uncertain, and no effects of intervention on adverse events were found. A small reduction in the stay and total hospital costs (silver-level evidence) was found [42]. However, very few studies have explored the feasibility of conducting exercise programmes for hospitalized acute elderly patients [43]. Furthermore, evidence is lacking to determine which types of hospitalized elderly patients would benefit more from each programme and whether each programme is viable.

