## Study design and setting

This study is a randomized clinical trial conducted in the Department of Geriatrics of a tertiary public hospital with 35 beds allocated. Hospitalized patients who meet the inclusion criteria will be randomly assigned to the intervention or control group. Patient recruitment will begin within the first 48 h of admission to the ward, and these patients will be identified through a list of patients admitted to the hospital and assigned to the Department of Geriatrics. The study flow diagram is shown in Fig. 1. After signing an informed consent form, the subjects will be randomly assigned (as explained below) to either the intervention or control group. The researcher who decides whether the patient is assigned to the intervention or control group will not be the attending physician. Patients or their relatives (if the patient has cognitive impairment) will be informed of the random inclusion in one group, but will not be informed as to which they belong. The data for both the intervention group and the control group will be obtained at four different times: the initial visit during the acute hospitalization, at discharge, and at one and three months after discharge from the outpatient clinic. Time of measurement of the different variables is shown in Table 1. The protocol employs relevant standard protocol items for clinical trials according to the SPIRIT 2013 statement [44] and follows the CONSORT statement [45] for transparent reporting. The trial is registered at ClinicalTrials.gov, identifier NCT02300896.

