### Intervention group (training)

The intervention will consist of a multicomponent exercise training programme [46], which will be composed of supervised progressive resistance exercise training, balance-training, and walking for 5–7 consecutive days. During the training period, patients will be trained in 20 min sessions twice a day (morning and evening).

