	Chet press	1RM + 1×10 (30 % 1RM)	2×10 (30 % 1RM)	3×10 (40 % 1RM)	3×10 (50 % 1RM)	3×8 (60 % 1RM)	3×8 (60 % 1RM)	3×8 (60 % 1RM)
	Leg extension	1RM + 1×10 (30 % 1RM)	2×10 (30 % 1RM)	3×10 (40 % 1RM)	3×10 (50 % 1RM)	3×8 (60 % 1RM)	3×8 (60 % 1RM)	3×8 (60 % 1RM)
Afternoon	Leg extension (0,5 – 1,0 Kg)		2×10	2×10	2×10	2×10	2×10	2×10
	Leg flexion (0,5 – 1,0 Kg)		2×10	2×10	2×10	2×10	2×10	2×10
	Hip abduction (0,5 – 1,0 Kg)		2×10	2×10	2×10	2×10	2×10	2×10
	Hand grip ball		2×10	2×10	2×10	2×10	2×10	2×10

*In case that the patient is still hospitalized

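### The exclusion for a stay under 6 days is worded as an actual stay, which cannot be known before randomisation; it should be an expected stay, judged beforehand

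*Protocol article*

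**What the plan says.** The exclusion list in Study participants and eligibility criteria opens with "Duration of hospitalization < 6 days". It does not say that the stay is expected or anticipated. The next item in the list, on factors that prevent training or testing, is expressly left to the attending physician's judgement.

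Study design and setting gives the timing: "Patient recruitment will begin within the first 48 h of admission to the ward", and "After signing an informed consent form, the subjects will be randomly assigned" to one of the two groups. No delay between consent and allocation is described.

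Training runs over "walking for 5–7 consecutive days" (Intervention group). In Table 2, days 6 and 7 carry the footnote "In case that the patient is still hospitalized".

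The Background links activity to length of stay twice. It says that longer walking or "daily slow walking can reduce the average hospital stay", and it reports of the review evidence on exercise in acutely ill older inpatients that "A small reduction in the stay and total hospital costs (silver-level evidence) was found".

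Statistics and sample size bases the calculation on the share of patients who gain more than 10 Barthel points at discharge: 161 per group, raised to 185 for a 15% loss in follow-up. Trial status ends recruitment once 370 patients have been randomised.

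**The concern.** An eligibility criterion should be decidable when the patient is allocated. A completed stay of under 6 days is a fact only at discharge, and here discharge comes after randomisation. Read literally, the rule can therefore act only as an exclusion after randomisation.

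That is a problem because the protocol's own background treats stay as something that walking or exercise may change. If the arms differ in how many patients leave before day 6, and if those patients differ in outcome from the rest, the patients who remain are no longer the groups that randomisation formed. Discharge is also when the sizing endpoint is measured, so the event that triggers the exclusion and the endpoint assessment coincide. Patients removed this way are not replaced, because the recruitment target counts those randomised.

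**Working it through.** **1. Order of events**

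| Step | When | Source |
|---|---|---|
| Recruitment starts | within 48 h of admission | Study design and setting |
| Randomisation | after consent, no wait described | Study design and setting |
| Training | 5–7 days; days 6 and 7 only if still an inpatient | Intervention group; Table 2 |
| Stay known to be under 6 days, or not | at discharge or on day 6 | Eligibility criteria |
| Sizing endpoint | at discharge | Statistics and sample size |

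The 6-day cut-off falls after allocation and inside or close to the training period.

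**2. The plan's own sample size.** Control rate, power and sidedness are not stated, so 161 has no unique derivation, but it is attainable. With p₁ = 0.29, p₂ = 0.44 (mean 0.365), two-sided 0.05, 80% power and no continuity correction:

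n = [1.960·√(2·0.365·0.635) + 0.842·√(0.29·0.71 + 0.44·0.56)]² / 0.15² = (1.334 + 0.566)² / 0.0225 ≈ 161.

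The stated 185 matches 161 × 1.15 = 185.15.

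**3. Patients lost if the rule is applied after randomisation.** After the planned loss, 185 × 0.85 = 157 per group. The extra share excluded is an assumption. Power is for an assumed 30% versus 45%, two-sided 0.05.

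| Extra share excluded | Analysed per group | Power |
|---|---|---|
| 0% | 157 | 79% |
| 10% | 157.25 × 0.90 = 142 | 74% |
| 20% | 157.25 × 0.80 = 126 | 69% |

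**4. Can it bias, and which way?** Suppose 35% respond in both arms (no true effect), and an extra share d is dropped from the exercise arm whose response rate is q. The rate among those kept is (0.35 − d·q)/(1 − d).

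- d = 0.15, q = 0.70: (0.35 − 0.105)/0.85 = 0.288, a bias of −6.2 percentage points.
- d = 0.15, q = 0.20: (0.35 − 0.030)/0.85 = 0.376, a bias of +2.7 points (0.0265 before rounding).
- d = 0 or q = 0.35: no bias.

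The sign depends on who leaves early, and the documents do not say.

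**5. Illustrative simulation, every input assumed.** Two million patients per arm, log-normal stay with median 8 days and log-SD 0.45, 35% responders, outcome–prognosis correlation 0.5, no true effect, better prognosis going with shorter stay. Stays under 6 days are deleted.

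| Exercise shortens stay by | Dropped, control / exercise | Bias (points) at stay–prognosis correlation 0.3 to 0.7 |
|---|---|---|
| 0 days | 26% / 26% | none |
| 0.5 day | 26% / 32% | −0.5 to −1.2 |
| 1 day | 26% / 38% | −1.0 to −2.4 |
| 2 days | 26% / 50% | −1.9 to −4.5 |

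At zero correlation, or with every randomised patient kept, the difference stays within 0.1 point of zero. The negative sign here follows from the assumed link between prognosis and stay.

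**The case against.** The strongest reply is that the authors meant a forecast made at screening. The item stands in an eligibility list, the article says that patients who meet the criteria are then randomised, and change is to be computed for every patient. Nothing states that a randomised patient is removed. On that reading there is no selection after randomisation. This is plausible, and it rules out saying that the plan deletes randomised patients. It does not rescue the wording: the neighbouring item is expressly a physician's judgement and this one is not, so the text as it stands permits the harmful reading.

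Four further inferences are tempting but not supported:

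- **Exercise will shorten stay materially.** The Background says only that walking can do so, and that the review found a small reduction. Length of stay is not a listed outcome.
- **Ward staff could hold back discharges to keep patients in.** Only the training staff are said to be impossible to blind. The article does not say whether ward staff know the allocation.
- **The lack of an analysis-population statement is itself a fault.** An article commonly leaves that to the full protocol or the SAP.
- **The rule fails to secure the training exposure.** A patient enrolled at 48 h with a 6-day stay has 6 − 2 = 4 days left, against at least 5 planned. That is the worst case, since enrolment may be earlier, and it is a scheduling matter rather than a bias.

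**Conclusion.** The point holds as a badly fixed eligibility rule. As worded, the criterion cannot be verified at allocation, and literal use would exclude randomised patients on a variable that treatment may affect.

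Bias needs three things together: the rule is applied after randomisation, stay (or the discharge decision) differs by arm, and stay is related to outcome. If any one is absent there is no bias, although literal use would still lose patients. A reader might infer from the simulated figures that the exercise effect will be understated by a known amount. The documents do not support that: they give no distribution of stay, no effect on stay of stated size and no link between stay and outcome. The simple arithmetic allows either sign. The bias figures show only that the mechanism works. The loss of numbers is firmer in kind, because the target counts randomised patients and no allowance is made beyond 15%, but the share lost is again an assumption.

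**What to change.** Reword the exclusion as an expected stay of less than 6 days, judged and recorded before randomisation. Add that a randomised patient whose actual stay turns out shorter is not excluded but remains in the assigned group, with the discharge assessment already planned for both groups.

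The cost is two sentences by amendment and no new measurement. Some patients will receive fewer training days than planned, which dilutes the effect slightly. In return, eligibility is settled before allocation, and early discharge no longer reduces the number analysed.

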### Randomization and blinding

The study participants will be randomized (www.randomizer.org) into an intervention group and a control group. Participants will be explicitly informed and reminded not to discuss their randomization assignment with the assessment staff. The assessment staff will be blinded to the participant randomization assignment, as well as to the main study design and to what changes we expect to occur in the study outcomes in either group.

It will not be possible to conceal the group assignment from the staff involved in the training of the intervention group.

Patients or their families (if the patient has cognitive impairment) will be informed of the random inclusion in one group, but will not be informed as to which group they belong.

### Statistics and sample size

The required simple size to detect a difference of 15 % in the frequency of patients that get at discharge a functional improvement greater than 10 points in Barthel Index is 161 patients in each group. Assuming a loss of 15 % of patients in the follow-up, we fixed a final sample size of 185 patients per group.

In an initial descriptive analysis, for qualitative variables we will calculate frequencies and confidence intervals, and for continuous variables, statistics of central tendency and dispersion such as means, standard error and confidence intervals or median and interquartile range. In order to assess the extent of the therapeutic effect, we will compute for every patient the difference between final and initial level of the outcome variables. Normality of continuous variables will be checked graphically and through K-M and Shapiro-Wilk tests, and their differences between groups by means of parametric tests (T-Tests, ANOVA) or non-parametric tests (Mann–Whitney U, Kruskal- Wallis). A Bonferroni post-hoc test will be used to evaluate statically significant (*p* < 0.05) group and time differences. Associations between clinical and biomechanical tests will be reported by their correlation coefficient (r value), level of significance (p value), and the amount of variance explained (r2 value). Values of r will be used to indicate small (r = 0.10), medium (r = 0.30), and large (r = 0.50) size correlations (i.e., effect size). Finally, the relationship between qualitative variables will be assessed through χ^2^ and Fisher exact tests. The level of statistical significance will be 0.05. Data will be analyzed with SPSS package 21.0

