**Fig. 1 Fig1:**
[figure not shown]
Flow diagram of the study protocol

**Table 1 Tab1:** Time of measurement of the different variables on the participants of the study

Measurement	T1 Baseline	T2 After training or control period	T3 1-month	T4 3-months
Categorical scale of pain	X	X	X	X
Barthel Index	X	X	X	X
Geriatric depression Scale of Yasavage	X	X	X	X
Mini-Mental State Examination (MMSE)	X	X	X	X
Short Physical Performance Battery (SPPB)	X	X	X	X
Gait Velocity Test (GVT)	X	X	X	X
Dual-task (verbal and counting GVT)	X	X	X	X
Maximal isometric force of handgrip, knee extension and hip flexion	X	X	X	X
1RM (Leg press, Chest press and Knee extension)	X	X	X	X
Muscle power at 50 % 1RM in Leg press	X	X	X	X
Confusion Assessment Method (CAM)	X	X	X	X
Quality of Life (EQ-5D)	X	X	X	X
Geriatrics syndromes	X	X	X	X
Isaacs set test	X	X	X	X
Trail Making Test (TMT)	X	X	X	X
Laboratory parameters	X			
Diseases considered grouped by ACG of Salisbury and CIE-10 codes	X			
Cumulative Illness Rating Scale for Geriatrics (CIRS-G)	X			
Zarit Scale	X			
Falls	X	X	X	X
Mini Nutritional Assessment (MNA)	X			

Adverse events, including muscle pain, fatigue, and general aches and pains will be recorded by the training and testing staff and by self-report during the study period. We will also record the number of falls during the study and for one year prior to admission.

This study has been approved by the Navarra Clinical Research Ethics Committee (Pyto 23/2014).

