### Outcome measures

#### Primary outcome

The primary outcome measure is the change in functional and cognitive status during the study period. The functional capacity of patients will be evaluated by the Short Physical Performance Battery (SPPB) [47], which evaluates, balance, gait ability, and leg strength using a single tool. The total score will range from 0 (worst) to 12 points (best). The SSPB test has been shown to be a valid instrument for screening frailty and predicting disability, institutionalization, and mortality. A total score of less than 10 indicates frailty and a high risk of disability and falls. One-point change in the score has clinical relevance [48, 49]. Loss of handgrip of the dominant hand is a useful tool for the measurement of functional capacity. It is a strong predictor of disability, morbidity, and mortality as well as one of the components of Fried’s frail phenotype. Furthermore, the functional status of patients will also be assessed before measurements with the Barthel Index, an international and validated tool of disability. The scores range from 0 (severe functional dependence) to 100 (functional independence) [50]. Gait ability will be assessed using the 6-metre gait velocity test (GVT). Starting and ending limits will be marked on the floor with tapelines for a total distance of 8 m. Participants will be instructed to walk in their self-selected usual pace for two attempts. The results of both trials will be averaged to obtain a single value. The first and last metre, considered the warm-up and the deceleration phases, respectively, will not be included in the calculations of the gait assessment. Dual task conditions (gait evaluation during the simultaneous performance of a cognitive motor action) have recently been recognized as a sensitive assessment method for interactions between cognition, gait, falls and frailty. Changes of gait parameters (i.e., gait velocity and gait variability) while performing a dual task test (dual task cost) could be early predictors of falls risk (50) and useful tools for functional evaluations in frail elderly patients. Exercise can modify dual task cost and consequently fall risk and functional capacity (31). The dual-task paradigm [51] will be used in the 6-m habitual gait velocity test (GVT). Two trials will be performed to assess the gait velocity while performing a verbal or counting task (verbal GVT and counting GVT, respectively). During the verbal dual-task condition (verbal GVT), we will measure the gait velocity while participants are naming animals aloud. During the arithmetic dual-task condition (counting GVT), we will assess the gait velocity while participants are counting backward aloud from 100 by ones. The cognitive score will be measured by counting the number of animals named (dual-task with verbal performance) or determining how many numbers were counted backward (dual-task with arithmetic performance). Isometric upper (right hand grip) and lower limb (right knee extensors and hip flexors) muscle strength will be measured using a manual dynamometer. Maximal dynamic strength will be assessed using the 1RM test in the bilateral leg press, knee extension and bench press exercises using exercise machines (Exercycle, S.L., BH Group, Vitoria, Spain). In the first assessment, the subjects will warm up with specific movements for the exercise test. Each subject's maximal load will be determined in no more than five attempts, with a 3-min recovery period between attempts. After determination of the 1RM values, the subjects will perform ten repetitions at maximal velocity at intensities of 50 % of 1RM to determine the maximum power (w) and the loss of power during the ten repetitions in the leg press machine. The power will be recorded by connecting a velocity transducer to the weight plates (T-Force System, Ergotech, Murcia, Spain). During all neuromuscular performance tests, a strong verbal encouragement will be given to each subject to motivate them to perform each test action as optimally and rapidly as possible. Qualified fitness specialists will individually monitor and carefully supervise all training sessions and provide instruction and encouragement during all sessions. Distribution of the training sessions throughout the day should minimize cumulative fatigue and help to maintain adherence. Adherence to the exercise intervention programme will be documented in a daily register of sessions. Changes in cognitive-affective status after the intervention will be measured using the Mini Mental State Examination, Yesavage GDS and Trail Making Test (Table 3).

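### The sample size rests on a Barthel responder rate at discharge that is not a listed outcome, while the declared primary outcome fixes neither one instrument nor one time point

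*Protocol article*

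**What the plan says.** **Sizing.** Statistics and sample size (Protocol article) bases the size on a 15% difference in the "frequency of patients that get at discharge a functional improvement greater than 10 points in Barthel Index". The result is 161 per group, raised to 185 for 15% loss. Trial status sets the total at 370 randomised.

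**Primary outcome.** The Primary outcome section states: "The primary outcome measure is the change in functional and cognitive status during the study period". The instruments follow in one long paragraph. The first is SPPB ("The functional capacity of patients will be evaluated by the Short Physical Performance Battery (SPPB"), the only one given a relevance threshold: "One-point change in the score has clinical relevance". Handgrip, Barthel, gait velocity, dual-task gait, strength and power follow. MMSE, Yesavage GDS and Trail Making Test close the list for the cognitive-affective part. Table 3 assigns Barthel to functional status and SPPB to functional capacity.

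**Secondary outcomes.** These are quality of life, delirium, mortality, use of health resources and falls. A Barthel responder rate is not among them.

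**Time points.** Study design and setting lists four assessments for both groups: initial visit, discharge, and one and three months after discharge. Table 1 heads the second one "T2 After training or control period".

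**Analysis.** Statistics and sample size plans final-minus-initial differences compared by parametric or rank tests, and chi-square or Fisher tests for qualitative variables.

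**The concern.** A sample-size calculation should belong to the comparison the trial will be judged on. Here the two statements disagree in three ways.

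- **Endpoint.** The size uses a dichotomised Barthel gain that no outcome list contains. The primary outcome is a set of instruments covering function and cognition.
- **Scale.** The size uses a yes/no rate. The treatment effect is mainly described as a difference in level.
- **Time.** The size uses discharge. The primary outcome refers to the whole study period, which includes discharge, one month and three months.

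Two things are at stake. First, nothing in the article supports the power for SPPB or for the cognitive half of the primary outcome. Second, with many instruments and three follow-up times under one primary heading, and a sizing paragraph pointing to something else, the headline result could be picked after the data are seen. An analysis plan may add detail, but the article itself makes both statements and they do not match.

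**Working it through.** **1. The plan's own figure.** Control rate, power and sidedness are not stated, so 161 can only be checked for consistency. Reading the 15% as percentage points and alpha as two-sided 0.05, the pooled-variance formula per group is

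n = [1.960·√(2p̄(1−p̄)) + z_power·√(p₁(1−p₁) + p₂(1−p₂))]² / 0.15²

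- 80% power, 29% vs 44%: (1.960 × 0.6809 + 0.842 × 0.6725)² / 0.0225 = 160.5, so 161. By symmetry 56% vs 71% also gives 161.
- 90% power, 15% vs 30%: (1.960 × 0.5906 + 1.282 × 0.5810)² / 0.0225 = 160.8, so 161. By symmetry 70% vs 85% also gives 161.

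So 161 fits ordinary settings for the Barthel responder rate and is not shown to be wrong.

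**2. Allowance for loss.** 161 × 1.15 = 185.15, which matches the stated 185. After 15% loss, 185 × 0.85 = 157.25, so about 157 per group remain. Dividing instead, 161 / 0.85 gives 190.

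**3. Sizing endpoint beside the primary outcome.**

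| | Sample-size paragraph | Primary outcome section |
|---|---|---|
| Measure | Barthel | SPPB, handgrip, Barthel, gait, dual task, strength, MMSE, GDS, TMT |
| Form | Share gaining more than 10 points | Change in status |
| Time | Discharge | Study period |

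Counting those nine measures once each at the three follow-up times gives 9 × 3 = 27 baseline-to-follow-up comparisons that fit the primary wording. This is a low count, since strength and dual task each contain several tests.

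**4. What the planned size gives for SPPB.** The 1-point difference is the article's own relevance threshold. The SD of SPPB change is not in the document, so the values below are assumptions. Alpha is two-sided 0.05.

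- n per group for 80% power = 2 × (SD × 2.8016 / 1)²
- Power at 157 = Φ(1 / (SD × √(2/157)) − 1.960), with √(2/157) = 0.1129

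| Assumed SD of change | n per group, 80% power | Power at 157 per group |
|---|---|---|
| 2 | 63 | 99% |
| 2.5 | 99 | 94% |
| 3 | 142 | 84% |
| 3.5 | 193 | 72% |
| 4 | 252 | 60% |

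The SD at which 157 per group gives exactly 80% is 1 / (2.8016 × 0.1129) = 3.16.

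**5. Any continuous change.** The detectable standardised difference at 80% power is 2.8016 × √(2/n): 0.31 at 161 per group and 0.32 at 157.

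**6. If cognition stays co-primary.** With alpha split to 0.025 each (an assumption), a 1-point SPPB difference at SD 3 needs 172 per group. Power at 157 is then 76%. The detectable standardised difference rises to 0.348, so the SD limit for 80% power falls to 1 / 0.348 = 2.87.

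**The case against.** Several counter-arguments are sound and limit the point.

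- **Barthel is not foreign to the primary outcome.** It is in the Primary outcome section, and Table 3 makes it the measure of functional status, the term the primary outcome uses. A reader might infer that SPPB is the declared primary because it comes first and carries a threshold. The article does not say so. The defect is that no instrument is singled out.
- **The size is informative about power.** A reader might infer that 161 or 185 tells us nothing about the primary outcome. That goes too far: about 160 per group detects a standardised difference of roughly 0.31 to 0.32 on any continuous change.
- **The scale difference is partial.** A gain above 10 points is itself derived from a final-minus-initial difference, and the planned chi-square and Fisher tests would suit a responder rate.
- **The second assessment is the same in both arms.** The Table 1 heading might suggest end of training in one arm and discharge in the other, so that the arms are compared after different recovery times. Study design and setting puts it at discharge for both groups, and no text describes unequal timing. The heading is a loose label.
- **Barthel power at 157 cannot be stated firmly.** It depends on a control rate and a design power that the article does not give.

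What remains is that the sized responder rate is on no outcome list, the primary outcome picks no measure or time, and SPPB and cognition have no stated power.

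**Conclusion.** The point holds as an inconsistency to be corrected, not as evidence that the trial is too small. The stated size belongs to a Barthel responder rate at discharge. The declared primary outcome is a multi-instrument change over an unspecified part of follow-up. Even if Barthel is read as the functional measure, the responder form and the discharge time point are not in the primary outcome, and the cognitive part has no sizing.

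For SPPB alone, 370 randomised is adequate for a 1-point difference up to an SD of change of about 3.16, assuming two-sided 5%, 80% power and 15% loss. Above that it falls short, with 72% power at SD 3.5. These SDs are assumptions, so the article alone does not settle adequacy. Keeping cognition as co-primary with split alpha lowers the limit to about 2.87.

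**What to change.** Make these changes before any between-arm look at the data:

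1. Name one primary endpoint and one time point: baseline to discharge, the second assessment in Study design and setting. Either change in SPPB or the Barthel measure used for sizing would serve. Make Statistics and sample size and Primary outcome agree on it.
2. State where the cognitive outcome goes: secondary, or co-primary with a stated multiplicity rule. List the remaining instruments as secondary.
3. Restate the sample-size paragraph for the chosen endpoint: difference, SD or control rate, sidedness, power, and the power that 370 randomised (about 157 per group after 15% loss) provides.
4. Align the second time-point heading in Table 1 with discharge.

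**Cost.** Every measure named is already taken at all four assessments, so no visit or test is added. For SPPB as the only primary, no extra enrolment is needed up to an SD of about 3.16; a larger SD or a co-primary cognitive endpoint would need rechecking. The downside is small but real. Recruitment opened in March 2015, so this is a mid-recruitment amendment to the primary-outcome wording, and the other listed measures lose primary status.
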